#### 2.9.2. Secondary Indicators

*(1) Gait Analysis*. Recent studies have shown that DLS can affect patients' gait, which can reflect the functional activities of musculoskeletal muscle in patients with DLS. At present, 3D gait analysis has been used in the diagnosis, treatment, and rehabilitation of DLS. Previous studies have systematically studied the gait of DLS patients from the perspectives of spatiotemporal parameters, kinematics parameters, dynamics parameters, and surface electromyography. It is found that the abnormal movement mode of muscles may be the cause of the decline of hip and knee joint range of motion and lumbar compensatory movement in DLS patients during walking.

*(2) sEMG*. Muscles play an important role in overall dynamic stability during functional tasks. sEMG provides an effective method to evaluate muscle response, such as detecting the changes of trunk muscle activity during walking. sEMG records the neural electrical signals received by the muscle and reflects the activity state of the muscle to some extent through the amplitude and activation time of the electrical signals.

### 2.10. Data Management and Monitoring

Case report forms (CRF) include observation points, treatment points, outcome measures, adverse events, and safety assessments. The researchers will be required to fill in the relevant information in a timely and accurate manner according to the requirements of the CRF. All data obtained will be kept strictly confidential and will be stored electronically in a secured and restricted-access database. Participants will be randomly numbered, and other personally identifiable information will be removed.

### 2.11. Statistical Analysis

All statistical analyses will be performed using SPSS Statistics for Windows Version 23.0 (IBM Corp., Armonk, NY). The normality test will be applied to all data. The *t*-test will be used if the data fit the normal distribution; otherwise, the rank sum test will be used. Counting data will be compared using the chi-square test. The significance level will be set at *P* < 0.05 and the confidence interval at 95%.

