### 2.4. Sample Size Calculation

This is a randomized controlled trial design, and the primary outcome was that patients' lower back pain improved. Our early clinical observation with a small sample (10 cases) found that 10 days of the experimental group and the control group can reduce scores on the JOA scale by 3.41 ± 1.86 and 2.24 ± 1.67 points, respectively. When the significance test level is set to 0.05 and the test power is set to 0.9, the sample size is calculated as follows:(1)$$\begin{array}{c} N=2\times {\left[\frac{\left(Z_{\alpha /2}+Z_{\beta }\right)\times \sigma }{\delta }\right]}^{2}. \end{array}$$When *α* is 0.05 and *β* = 0.1, the normal distribution quantile table shows the following:(2)$$\begin{array}{c} Z_{\alpha /2}=1.96,\\ Z_{\beta }=1.282, \end{array}$$where *σ* and *δ* represent the population standard deviation and allowable error, which are 1.86 and 1.17, respectively. The result is 54 by plugging these data into the formula, so 54 patients will be needed in each group. Since there may be a 10% dropout rate, we will recruit 60 participants in each group for this study.

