### 2.6. Randomization

All included participants will be randomly assigned to the experimental group and the control group at a ratio of 1 : 1. This study will be randomized to generate a sequence of random numbers using randomization software, and a specialized statistician who is not a searcher in this study will be responsible for processing the results. Meanwhile, sequentially numbered and sealed opaque envelopes which reveal random numbers will be provided to the patients according to the order of the subjects' visits (the order of visits was consistent with the envelope number), and these envelopes will be hidden until informed consent is obtained.

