#### 2.9.1. Primary Index

*(1) Japanese Orthopedic Association Score (JOA)*. JOA is used to evaluate functional disorders [18]. The highest JOA score was 29, and the lowest was 0. Lower scores indicate greater dysfunction. The improvement index, the difference between posttreatment and pretreatment scores, can reflect the improvement of lumbar function before and after treatment. The clinical effect can be understood through the improvement rate (improvement rate is the ratio of posttreatment score minus pretreatment score to 29 minus pretreatment score). The improvement rate can also correspond to the commonly used therapeutic effect criteria: the improvement rate of 100% is cured, the improvement rate of more than 60% is effective, 25–60% is effective, and the improvement rate of less than 25% is ineffective.

*(2) Visual Analogue Scale (VAS)*. VAS is widely used in clinical pain assessment because of its simplicity and practicability [19]. The same method before and after clinical treatment can be used to objectively score and evaluate the effect of pain treatment. Participants looked at a walking scale and said a number between 0 (painless) and 10 (the worst pain to endure) instead of filling out a complex questionnaire. This method is simple, objective, and sensitive.

*(3) Oswestry Disability Index Score (ODI)*. ODI is often used to evaluate low back pain dysfunction [20]. The ODI scale consists of 10 parts, covering pain levels, personal care, lifting objects, walking, sitting, standing, sleep, sex life, social activities, and travel. The scores for each of the above 10 sections range from 0 to 5, with a maximum score of 50. The ODI index was obtained by dividing the patient's actual score by 50 and multiplying by 100%. The higher the ODI index, the more serious the patient's dysfunction.

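### The primary analysis is left to a normality test and does not adjust for baseline; a pre-specified baseline-adjusted ANCOVA would gain power at no cost

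*Protocol article*

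**What the plan says.** Section 2.11 gives one rule for all continuous outcomes: "The normality test will be applied to all data", and then a t-test "will be used if the data fit the normal distribution; otherwise, the rank sum test will be used". It sets the significance level at 0.05 and the confidence interval at 95%. It does not name the normality test, its level, or whether it is run per arm or pooled. It names no covariate and does not say which score enters the comparison.

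Section 2.9.1 lists JOA, VAS and ODI as primary. For JOA it defines a change score: "The improvement index, the difference between posttreatment and pretreatment scores". It also describes VAS scoring before and after treatment. It gives no timing for ODI, and 2.9.2 gives none for gait or sEMG.

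Section 2.4 sizes the trial on JOA change. The arms "can reduce scores on the JOA scale by 3.41 ± 1.86 and 2.24 ± 1.67 points, respectively", and the two planning values "represent the population standard deviation and allowable error, which are 1.86 and 1.17, respectively".

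**The concern.** Two features of the rule deserve attention.

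- **Baseline.** Pre-treatment JOA and VAS scores are collected, but the stated tests use them at most by subtraction. Adjusting for baseline as a covariate is never less precise in large samples than either the change or the post-treatment score alone. Because 2.11 does not choose between those two, it also permits the weaker one.
- **The gate.** The data decide whether the primary result is a comparison of means, on which the trial was sized, or a comparison of ranks. The three primary measures could take different branches. On a coarse scale, the normality test may also react to the scoring grid and not to any real departure from normality.

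At stake are precision already paid for and a primary method that is unknown until the data are seen.

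**Working it through.** **Inputs**
- From 2.4: two-sided alpha 0.05, power 0.90, difference 1.17, SD of JOA change 1.86, 54 evaluable per arm.
- From 2.6: 1:1 allocation.
- Assumed, because the document gives no figure: pre-post correlation r of 0.3, 0.5, 0.7 or 0.8; equal pre and post variances; whole-point JOA scoring; Shapiro-Wilk at 0.05 in each arm.

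**1. The plan's own figure.** n = 2 × [(1.96 + 1.282) × 1.86 / 1.17]² = 53.13, rounded up to 54 per arm. With 10% dropout, 54 / 0.9 = 60. Both stated numbers reproduce.

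**2. t-test on change.** The standard error is 1.86 × √(2/54) = 0.358, and 1.17 / 0.358 = 3.27. Power is 90.0% from the noncentral t distribution (90.5% by the normal approximation). The planned power is met.

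**3. The alternatives.** Let s be the common SD of the pre and post scores. The variance of change is 2s²(1 − r), so s = 1.86 / √(2(1 − r)). The ANCOVA residual variance is s²(1 − r²) = 1.86² × (1 + r)/2. Power at 54 per arm, from the noncentral t:

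| r | ANCOVA SD | ANCOVA power | Change-score t-test | Post-only SD | Post-only t-test |
|---|---|---|---|---|---|
| 0.3 | 1.50 | 98.0% | 90.0% | 1.57 | 96.9% |
| 0.5 | 1.61 | 96.2% | 90.0% | 1.86 | 90.0% |
| 0.7 | 1.71 | 94.0% | 90.0% | 2.40 | 70.8% |
| 0.8 | 1.76 | 92.7% | 90.0% | 2.94 | 53.5% |

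ANCOVA gains about 3 to 8 points over the change-score test. By the normal approximation it would need 35, 40, 46 or 48 per arm for 90% power, instead of 54.

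**4. What the gate does to the result.** This was simulated with 4,000 trials, 54 per arm, r = 0.5, and baseline and post scores both rounded to whole points.
- Power at a difference of 1.17: t-test on change 88.6%, rank-sum 87.2%, two-stage rule 87.6%, ANCOVA 96.0%.
- Type I error of the two-stage rule: 4.5%.
- The t-test and rank-sum test disagree on significance in about 3% of trials.

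The switch therefore costs 88.6 − 87.6 = 1.0 point and does not inflate type I error.

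**5. What rounding does to the choice of test.** Truly normal JOA changes with SD 1.86, rounded to whole points, are rejected by Shapiro-Wilk in at least one arm in about 75% of trials (73% to 78% across separate runs). For unrounded data the figure is about 10%. The effect fades as the SD grows relative to the rounding unit: about 26% at SD 3, 14% at SD 5 and 11% at SD 7.

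**The case against.** Four objections carry weight.

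- **Baseline is not ignored for JOA.** A reader might infer from the absence of a covariate that baseline scores go unused. The document does not support that. The sample size and the improvement index both work with change, so baseline may enter by subtraction. Under randomisation that analysis is valid and unbiased, and it meets the planned 90%. What stands is that baseline is not adjusted for as a covariate, and that 2.11 does not fix which score is tested.
- **The pre-test is not what costs the power.** A reader might attribute the whole loss to the normality test. The switch accounts for about 1 point; the rest comes from not adjusting. The size of that gain depends on a correlation the document does not give, although ANCOVA is ahead at every value in the range.
- **Rounding is shown for JOA only.** It is tempting to say that rounding will choose the test for every outcome. That needs whole-point scoring, a particular normality test and a small SD. ODI has a raw range of 0 to 50 and no stated SD, and gait and sEMG are instrument measurements. The document gives no basis for extending the claim to them.
- **A rank-sum test can carry an interval.** A Hodges-Lehmann interval accompanies it, and under a pure shift model it estimates the same shift as the mean difference. The estimands separate only outside that model.

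It can also be said that a condensed article may leave covariates to a SAP that is not shown. That would excuse silence. Here the article states a rule, and the rule itself can be improved.

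**Conclusion.** The point holds as a free improvement. As written, 2.11 leaves the primary test and its effect measure to a normality test and names no baseline adjustment. Under the assumptions listed, ANCOVA would raise power for JOA at 54 per arm from 90% to between 93% and 98%. It would also rule out a comparison of post-treatment scores alone, whose power falls to 71% at r = 0.7 and 54% at r = 0.8. The gate does little harm to power or type I error; its fault is that the method is not fixed in advance. Rounding could decide the choice of test for JOA in about three trials in four, but it would seldom change the significance verdict. The document does not support a claim that the trial is underpowered or that the change-score analysis is biased.

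**What to change.** In 2.11, replace the two-step rule as follows.

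- For JOA and VAS, and for ODI, gait and sEMG measures where a baseline is taken, pre-specify an ANCOVA of the end-of-treatment score on arm and the baseline score of the same measure.
- Report the adjusted mean difference with its 95% CI.
- Drop the normality test as gatekeeper.
- Keep the rank-sum test as a sensitivity analysis.

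The cost is a few lines of text. The model runs in the SPSS version named in 2.11. For JOA and VAS no new data are needed, and the sample size can stay as it is.

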### 2.12. Withdrawal and Dropout

The subject will be excluded from the study if the subject does not meet the inclusion and exclusion criteria or withdraws his/her consent, or the subject's continued participation is judged as inappropriate. The researchers will record the reason for any interruption in the intervention and whether each participant completed the study.

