### 2.7. Blinding

Due to the limitations of acupuncture treatment, the acupuncturists cannot be blinded to who will be informed of the grouping of participants before treatment. The outcome evaluators and data statisticians will be blinded to the group allocation to improve the quality of this study as much as possible. In addition, participants will be assigned to different rooms during the treatment to avoid exchange from each other. Therapists, data managers, and statisticians are not allowed to communicate with others about the treatment of patients.

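### Sections 2.3 and 2.12 let participants be excluded after randomisation for events during treatment or on an undefined judgement, and nothing keeps them in follow-up

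*Protocol article*

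**What the plan says.** Section 2.12, headed as dealing with withdrawal and dropout, says: "The subject will be excluded from the study if the subject does not meet the inclusion and exclusion criteria or withdraws his/her consent". It continues with a third ground, that "the subject's continued participation is judged as inappropriate". The rule is not limited to the period before randomisation, and no decision-maker or criteria are given for the third ground. The section does require the reason for any interruption of treatment, and whether each participant completed, to be recorded.

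The last exclusion criterion in section 2.3 covers combination medication or participation in another trial during the treatment period. Prior treatment is dealt with separately, in the inclusion criteria of section 2.2.

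Section 2.7 says that "the acupuncturists cannot be blinded to who will be informed of the grouping of participants before treatment", and that "The outcome evaluators and data statisticians will be blinded to the group allocation". It does not list participants among those blinded. Section 2.15 has two supervisors check eligibility and adherence to the trial process, and has drop-outs, withdrawals and compliance recorded.

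Section 2.11 gives the tests: "The *t*-test will be used if the data fit the normal distribution; otherwise, the rank sum test will be used". It names no analysis set. Section 2.4 plans 54 per group and recruits 60 to allow for 10% dropout.

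**The concern.** Randomisation protects a comparison only if the people compared are those who were randomised. Here a written rule can take people out afterwards, and at least one trigger, starting other treatment, may itself follow from how well the assigned treatment is working. The judgement ground is open-ended, and some of the staff around the participant know the allocation. If removal is related to outcome and is more frequent or more selective in one arm, the JOA, VAS and ODI comparisons are all distorted, in a direction that cannot be known in advance.

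The wording in section 2.12 is exclusion from the study. Followed literally, that plausibly ends outcome assessment. Blinded evaluators do not help if the participant never reaches them, and no later analysis plan can recover outcomes that were not collected.

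**Working it through.** **Reproducing the plan's own figure.** Section 2.4 sets the design values: "When the significance test level is set to 0.05 and the test power is set to 0.9", with σ and δ that "represent the population standard deviation and allowable error, which are 1.86 and 1.17, respectively".

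- n per group = 2 × [(1.96 + 1.282) × 1.86 / 1.17]² = 53.1, rounded up to 54.
- With 10% dropout: 54 / 0.9 = 60.

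Both figures reproduce. Power for 1.17 points at SD 1.86 is 93.1% with 60 per group, 90.5% with 54 and 86.9% with 48. Loss of numbers within the allowance is therefore covered. The issue is bias.

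**Is exclusion after randomisation really stated?**

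- The medication and other-trial criterion in 2.3 refers to the treatment period. Treatment follows randomisation, so nobody can meet it at screening.
- Section 2.12 excludes anyone who fails the criteria, and its third ground concerns continuing in the trial. Both fit its heading, which is about leaving the trial after entry.
- No sentence in 2.11, 2.12 or 2.15 says that such participants go on being assessed.

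**Size, illustration A (pilot gains).** The inputs are the 10-day JOA changes in section 2.4, 3.41 and 2.24, read as improvements. Assumptions: these are the gains of those retained; a fraction f = 10% is removed; those removed had no gain. The all-randomised mean of an affected arm is then (1 − f) × retained mean. The retained participants always show 3.41 − 2.24 = 1.17.

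- Both arms lose 10%: 0.9 × 3.41 − 0.9 × 2.24 = 3.069 − 2.016 = 1.053. Overstatement 1.17 − 1.053 = 0.117, or 10% of 1.17.
- Experimental arm only: 3.069 − 2.24 = 0.829. Overstatement 0.341, or 29%.
- Control arm only: 3.41 − 2.016 = 1.394. Understatement 0.224, or 19%, in favour of control.
- Removal balanced and unrelated to outcome: no bias.

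**Size, illustration B (no true difference, SD 1.86).**

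- If those removed lie on average 1 SD below their arm's mean, the retained mean rises by f/(1 − f) × 1.86. With 15% removed in one arm and 5% in the other: 0.15/0.85 × 1.86 − 0.05/0.95 × 1.86 = 0.328 − 0.098 = 0.23 points, about 20% of 1.17.
- Worst case, the poorest responders are removed from one arm only. The retained mean rises by 1.86 × φ(z)/(1 − f), where φ is the standard normal density and z is the normal quantile at f. For f = 5%, 10% and 15% this gives 0.20, 0.36 and 0.51 points (17%, 31% and 44% of 1.17), with two-sided type I error of about 9%, 20% and 36%.
- Equal and similarly selective removal in both arms gives no shift when there is no true difference.

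**The case against.** A reader might infer more than the text supports, and several stronger readings should be set aside.

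- *That the comparison is a completer analysis.* The article does not say so. It names no analysis set, and exclusion from the study need not mean exclusion from the analysis. Analysis populations are commonly left to a full protocol or analysis plan, neither of which is shown, so their absence here is no fault.
- *That raising 54 to 60 shows only completers are analysed.* It does not. Allowing for lost outcomes is equally normal under intention-to-treat.
- *That unblinded staff make the exclusions.* No judge is named. The acupuncturists know the arm, but nothing says that they decide, and the blinding of the two supervisors is not stated.
- *That the criterion is about pain medication and marks poor response.* Section 2.3 refers to combination medication without naming a type. A link with response is plausible but is not a fact from the document.
- *That all the grounds in 2.12 are faulty.* Withdrawal of consent is a right confirmed in section 2.14. Ineligibility found late may rest on baseline facts and need not relate to outcome.

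It is also fair that the 0.34-point figure is a one-arm scenario that spends the whole 10% dropout allowance on outcome-related removal.

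What the objection does not remove is the rule itself. Exclusion for events during treatment and on an undefined judgement is written into the article. It is not something merely left unsaid, and an analysis plan could define an analysis set but could not supply outcomes that were never measured.

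**Conclusion.** The point holds as a defect in the exclusion rule. Sections 2.3 and 2.12 together make post-randomisation events, late-found ineligibility and an unspecified judgement grounds for leaving the study, with no provision for continued follow-up. Followed as written, the rule can remove participants in a way related to outcome and different by arm.

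Under the assumption of 10% removal with no gain, the JOA difference is overstated by about 0.12 points with equal loss and by 0.34 points with loss in the experimental arm alone. Loss in the control arm alone understates it by about 0.22 points. How many would be removed, and how their outcomes would compare, cannot be read from the article, so these figures show scale and are not predictions.

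**What to change.** Reconcile sections 2.3 and 2.12 as follows.

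1. State that eligibility criteria are applied before randomisation only. Whether other treatment is permitted during the trial is a clinical matter for the investigators. The change concerns only what its use does to follow-up and analysis.
2. Record medication use, participation in another trial, late-found ineligibility and stopping of treatment as events or protocol deviations.
3. In 2.12, replace exclusion from the study with continued outcome collection on schedule, ending only if the participant withdraws consent to it. State who may judge continued participation inappropriate, and on what grounds.
4. State that all randomised participants are analysed in their assigned group, with completers as a sensitivity analysis.

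The cost is a change of wording and a few extra outcome assessments. Gait analysis and sEMG need attendance, so for those measures a telephone contact will not do. The effect estimate may be slightly diluted by participants who stopped or added treatment. The sample size need not change on this account.

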### 2.13. Safety

The occurrence of all adverse events will be assessed at each visit. Subjects will be monitored for undesirable, unintended symptoms, signs, and illnesses. The number and percentage of subjects who experience at least 1 adverse event will be calculated. To ensure the safety of participants, the data collection process will be supervised by the project leader. At each visit, participants will be required to stay in the hospital for 30 minutes after treatment and will be asked about any adverse events during the study that showed signs of acute adverse events. Adverse effects will be recorded at each visit during treatment.

### 2.14. Ethics

This study is designed based on the principles of the Helsinki declaration and has been approved by the Ethics Committee of the First Affiliated Hospital of Henan University of Chinese Medicine (2021HL-192). After careful discussion and modification by the project team, the protocol is registered on the website of the Chinese Clinical Trial Registry (ChiCTR) (ChiCTR2100050409). Participants will be informed of the possible risks and other related matters of the study protocol before entering the study and will sign an informed consent before randomization. All participants of this study will be allowed to withdraw their consent at any time for any reason.

